### Cycles 2, 3 and 4: Day 1 of chemotherapy cycle

| T(hrs)  |                                                                                |                                                                                                                                                 |                                                    |
|---------|--------------------------------------------------------------------------------|-------------------------------------------------------------------------------------------------------------------------------------------------|----------------------------------------------------|
| T 0     | Pre-meds                                                                       | paracetamol 1g po
ranitidine 150mg po
iv chlorphenamine 10mg,
iv bolus dexamethasone 8 mg
iv bolus ondansetron 8 mg (or equivalent) | flush line with
normal saline
(not dextrose) |
| T 0 - 1 | cetuximab
250mg/m                                               | (weeks 2 to 12)                                                                                                                                 | IV infusion
over 1 hours                        |
| T 0 - 2 | Patients should be monitored for hypersensitivity reaction to cetuximab |                                                                                                                                                 |                                                    |
| T 1 - 2 | pre-hydration                                                                  | Furosemide 40mg IV bolus or po*sodium chloride 0.9% (normal saline) 1 litre
+ 20mmol KCl + 10mmol MgCl 2                          | IV infusion
over 1 hour                         |
| T 2 - 4 | cisplatin
60mg/m                                                | In sodium chloride 0.9% (normal saline) 1 litre
concurrently with mannitol 10% 200ml                                                         | IV infusion
over 2 hours                        |
| T 4 - 6 | Post-hydration                                                                 | Sodium chloride 0.9% (normal saline) 1 litre
+ 20 mmol KCl + 10mmol MgCl 2                                                        | IV infusion
over 2 hours                        |
| T 6 - 7 | Post-hydration**                                                               | Sodium chloride 0.9% (normal saline) 500mL
+ 10 mmol KCl                                                                                     | IV infusion
over 1 hour                         |

Patients should be advised to drink 2 litres of fluids over the next 24 hours.

\*Furosemide may be used in some centres, as per their usual practice, to increase urine output. However Furosemide is a potentially ototoxic drug and thus may increase the risk of ototoxicity with cisplatin.

\*\*This final 500mls of post-hydration may be omitted if the patient is able to drink 500mls after the cisplatin.

### Day 8 and 15 of each chemotherapy cycle

| T(hrs)  |                                                                                |                                                                                                    |                                                    |
|---------|--------------------------------------------------------------------------------|----------------------------------------------------------------------------------------------------|----------------------------------------------------|
| T 0     | Pre-meds                                                                       | paracetamol 1g po
ranitidine 150mg po
iv chlorphenamine 10mg,
iv bolus dexamethasone 8 mg | flush line with
normal saline
(not dextrose) |
| T 0 - 1 | cetuximab
250mg/m                                               |                                                                                                    | IV infusion
over 1 hour                         |
| T 0 - 2 | Patients should be monitored for hypersensitivity reaction to cetuximab |                                                                                                    |                                                    |
| T 1     |                                                                                |                                                                                                    | flush line with
normal saline
(not dextrose) |

### Day 1, Weeks 3 and 4

The first fraction of radiotherapy must be given after the cisplatin has been administered on Day 1 of chemotherapy cycles 3 and 4. Radiotherapy may be given during the post-hydration which may need to be interrupted for a short period of time.

## **6.3 Non trial treatment in the research arm**

### **6.3.1 Medications permitted**

Pre-medication with an antihistamine is required to protect the patient in the event of a hypersensitivity reaction to cetuximab.

Pre-medication with steroids such as dexamethosone, analgesic (e.g. paracetamol), anti-emetic (e.g. granisetron, ondansatron) and H2 blockers (e.g. ranitidine) are recommended prior to trial treatment.

### **6.3.2 Medications permitted with caution**

The following drugs have been shown to possibly have some interaction with cisplatin and may require dose modification:

- Ototoxic drugs like aminoglycoside antibiotics or loop diuretics (e.g. furosemide), may increase ototoxic potential of cisplatin.
- Anti-epileptics; the serum level of phenytoin may be reduced and levels should be monitored and the dose adjusted accordingly.
- Reduce renal excretion of bleomycin and methotrexate which increases their toxicity.
- Anti-gout agents (like allopurinol, colchicine, probenecid or sulfinpyrazone).

The following drugs have been shown to possibly have some interaction with Pyrimidine analogues like capecitabine or 5FU and may require dose modification:

- Coumarin derivative anticoagulants (like warfarin) require more frequent monitoring due to altered coagulation parameters, and effects may occur up to several months after initiating capecitabine therapy.
- There can also be interactions with cytochrome P-450 (isozymes 1A2, 2C9 and 3A4).
- Allopurinol (reduce the efficacy of 5FU).
- Phenytoin plasma levels may be increased, levels should be regularly monitored.

### **6.3.3 Non permitted medications**

Cetuximab has no known interactions with concomitant medications.

The following drugs have been shown to interact with cisplatin and should be avoided if possible:

- Cumulative nephrotoxicity may be potentiated by aminoglycoside antibiotics e.g. gentamicin. These should not be administered, if possible, simultaneously or 1-2 weeks after treatment with cisplatin.
- Cisplatin can also react with aluminium and all aluminium containing IV sets, needles, catheters and syringes should be avoided.
- The solution for infusion should not be mixed with other drugs or additives.

The following drugs have been shown to have some interaction with pyrimidine analogues like capecitabine or 5FU and should be avoided:

- Sorivudine and analogues (would require a 4-week wash out prior to entering in the trial)
- Aluminium hydroxide or magnesium hydroxide containing antacids.
- Methotrexate is not recommended with any form of chemotherapy.

## **7. CLINICAL CONSIDERATIONS**

### **7.1 Pregnancy**

Patients should be advised that contraception should be used where applicable to avoid the possibility of pregnancy occurring to themselves, or their partners, due to the potentially harmful effects of chemo-radiation. In the very unlikely event that a pregnancy occurs patients should be advised to report this to their treatment centre immediately. The PI is responsible for reporting this information to the WCTU immediately and the pregnancy should be followed up according to guidance by the WCTU who will apply the MHRA pharmacovigilance recommendations.

### **7.2 Nutritional status**

Patients with oesophageal cancer may have a poor nutritional status and centres should be aware that good clinical practice would normally include a basic dietician review. Patients within the trial would be expected to receive the same nutritional support as those not included, and that where there is a clinical need for invasive enteral nutrition, such as insertion of a PEG, this is permitted, and data will be collected to confirm the rate of enteral nutritional required.

### **7.3 DPD deficiency**

Occasionally (approximately 1-3%) a patient may have a markedly exaggerated toxicity due to reduced 5FU catabolism. If this occurs, await full recovery of toxicities. Further treatment should be carried out at a much reduced capecitabine dose (e.g. 50%). Please discuss with the Chief Investigator or one of the clinical co-investigators as required.

## **8. DRUG SUPPLY, DOSING, SIDE EFFECTS AND MODIFICATIONS**

Chemotherapy should only be administered under the direction of Oncologists in specialist units under conditions permitting adequate monitoring and surveillance. Supportive equipment should be available to control anaphylactic reactions.

### **8.1 Drug Supply**

#### **8.1.1 Cisplatin and Capecitabine (5FU)**

Cisplatin, capecitabine and 5FU (when used in place of capecitabine) shall be available through routine medical supplies. Patients will be asked to bring any remaining tablets to their next visit so that they can be counted for drug accountability and concordance. Patient diaries will also be used to check concordance.

#### **8.1.2 Cetuximab**

Cetuximab is not licensed for this indication and drug supply will be from stock supplied by Merck KGaA. Cetuximab is provided in ready to use vials at a concentration of 5mg/mL. Details of storage and preparation of cetuximab are available as part of the drug packaging and in cetuximab's Summary of Product Characteristics (SPC).

Details of the procedures for obtaining cetuximab within the trial will be included in the SCOPE 1 pharmacy pack which will be sent to the pharmacy department of centres participating in the trial. The pack will include record sheets for drug accountability and cetuximab order forms. Stock will arrive labelled for 'Clinical trial use only'. Further drug supplies will be co-ordinated by hospital pharmacies directly with Merck KGaA using a drug request form.

Full drug accountability will be required for the cetuximab supplied to the pharmacy at the participating centres. Pharmacists will be required to document the receipt, dispensing, return and destruction of cetuximab.

Further details on the storage and preparation of cetuximab are available in the cetuximab SPC.

## 8.2 Dosing and precautions

Body Surface Area (BSA) should be calculated according to local policy. If required the formula and calculator are available at <http://www.halls.md/body-surface-area/refs.htm>.

### 8.2.1 Cisplatin and capecitabine (5FU)

**Cisplatin** will be administered as a short intravenous infusion at 60mg/m^2 over 2 hours on treatment days with adequate pre- and post hydration and electrolyte correction (see treatment schedule). On days of concurrent chemo-radiation cisplatin should be completed before radiotherapy treatment. Patients may undergo their radiotherapy during the post-hydration following cisplatin, which may be interrupted provided it is completed afterwards.

Cisplatin 1 mg/ml Sterile Concentrate should be diluted in 1 litre of 0.9% sodium chloride injection. Cisplatin reacts with metallic aluminium to form a black precipitate of platinum. All aluminium containing IV sets, needles, catheters and syringes should be avoided. The solution for infusion should not be mixed with other drugs or additives

**Capecitabine** treatment is usually administered on an outpatient basis.

Oral capecitabine 625mg/m^2 twice a day (to the nearest achievable dose using 500mg and 150mg tablets). Patients will be asked to take the medication every 12 hours for example 8:00am / 9:00 am and 8:00 pm / 9:00 pm each day, within 30 minutes after eating.

If a patient vomits after taking the capecitabine tablets they should not take another dose. The next dose of capecitabine should be taken at the planned usual time.

#### Calculated capecitabine dose at dose level 625 mg/m^2.

| Dose Level 625 mg/m 
(twice daily) |                                    | Number of tablets
administered in the
morning |        | Number of tablets
administered in the
evening |        |
|---------------------------------------------------|------------------------------------|-----------------------------------------------------|--------|-----------------------------------------------------|--------|
| Body
Surface
Area
(m  )      | Dose per
administration
(mg) | 150 mg                                              | 500 mg | 150 mg                                              | 500 mg |
| ≤1.38                                             | 800                                | 2                                                   | 1      | 2                                                   | 1      |
| 1.39 – 1.52                                       | 950                                | 3                                                   | 1      | 3                                                   | 1      |
| 1.53 – 1.78                                       | 1000                               | -                                                   | 2      | -                                                   | 2      |
| 1.79 – 1.92                                       | 1150                               | 1                                                   | 2      | 1                                                   | 2      |
| 1.93 – 2.18                                       | 1300                               | 2                                                   | 2      | 2                                                   | 2      |
| ≥ 2.19                                            | 1450                               | 3                                                   | 2      | 3                                                   | 2      |

### Calculated capecitabine dose at dose level 75%

| 75% dose level
(twice daily) |                | Number of tablets
in the morning |       | Number of tablets
in the evening |       |
|---------------------------------|----------------|-------------------------------------|-------|-------------------------------------|-------|
| BSA                             | Dose per admin | 150mg                               | 500mg | 150mg                               | 500mg |
| ≤ 1.38                          | 650mg          | 1                                   | 1     | 1                                   | 1     |
| 1.39 – 1.52                     | 650mg          | 1                                   | 1     | 1                                   | 1     |
| 1.53 – 1.78                     | 750mg          | 5                                   | -     | 5                                   | -     |
| 1.79- 1.92                      | 800mg          | 2                                   | 1     | 2                                   | 1     |
| 1.93 – 2.18                     | 1000mg         | -                                   | 2     | -                                   | 2     |
| ≥ 2.19                          | 1150mg         | 1                                   | 2     | 1                                   | 2     |
|                                 |                |                                     |       |                                     |       |

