| Oesophagus | Definitive
CRT         | 31 | 18:13     | 9 (29)
G3 PPE x 3
G3 Mucositis x 5
G3 Neutropenia x 1
1 x DVT | 4 x dose reductions
4 x dose delay
2 x treatment
discontinued –PD
1 x treatment
discontinued –IHD |
| Stomach    | Post-
operative
CRT | 7  | 7:0       | 2 (29)
G3 neutropenia x 1
G3 PPE x 1                                |                                                                                                                  |

Abbreviations: PPE, Palmar-plantar erythema; DVT, deep vein thrombosis;  
PD, progressive disease; IHD, Ischemic Heart disease.

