### Calculated capecitabine dose at dose level 50%

| 50% dose level
(twice daily) |                | Number of tablets
in the morning |       | Number of tablets
in the evening |       |
|---------------------------------|----------------|-------------------------------------|-------|-------------------------------------|-------|
| BSA                             | Dose per admin | 150mg                               | 500mg | 150mg                               | 500mg |
| ≤ 1.38                          | 450mg          | 3                                   | -     | 3                                   | -     |
| 1.39 – 1.52                     | 500mg          | -                                   | 1     | -                                   | 1     |
| 1.53 – 1.78                     | 500mg          | -                                   | 1     | -                                   | 1     |
| 1.79- 1.92                      | 600mg          | 4                                   | -     | 4                                   | -     |
| 1.93 – 2.18                     | 650mg          | 1                                   | 1     | 1                                   | 1     |
| ≥ 2.19                          | 650mg          | 1                                   | 1     | 1                                   | 1     |
|                                 |                |                                     |       |                                     |       |

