## 8.4 Dose modifications

### 8.4.1 Cisplatin and capecitabine (or 5FU)

#### Haematological

The FBC should be taken and reviewed (up to 3 days) prior to Day 1 of each cycle of chemotherapy.

| Neutrophil / platelet count ( $10^9/L$ ) (day 1)                                                   | Action                                                                                                   |
|----------------------------------------------------------------------------------------------------|----------------------------------------------------------------------------------------------------------|
| ANC $\geq 1$ and/or plts $\geq 75$                                                                 | Full dose drugs                                                                                          |
| ANC 0.5- $<1$ and/or plts 50- $<75$ OR any episode of neutropenic sepsis during the previous cycle | Stop chemotherapy until recovery.
Restart with 25% dose reduction cisplatin and capecitabine (or 5FU) |
| ANC $<0.5$ and/or plts $<50$                                                                       | Stop chemotherapy until recovery.
Restart with 50% dose reduction cisplatin and capecitabine (or 5FU) |

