#### Nephrotoxicity

Cisplatin produces cumulative nephrotoxicity. If a baseline estimate of renal function using the Cockcroft & Gault formula predicts the GFR to be  $\geq 60\text{mL/min}$  full dose cisplatin should be used. If the estimate is  $<60\text{mL/min}$  an EDTA Creatinine clearance should be performed and the appropriate cisplatin dose used (see table below). In the case of a 25% deterioration in estimated renal function (using the Cockcroft & Gault formula) on pre-treatment blood samples an EDTA Creatinine clearance should be performed and pending this an appropriate dose reduction in cisplatin should be made. The EDTA Creatinine clearance result, when available, takes precedent over estimated GFR for subsequent cisplatin dose calculations.

| GFR (mL/min) Baseline and prior to Day 1 | Action                                                         |
|------------------------------------------|----------------------------------------------------------------|
| $\geq 50\text{mL/min}$                   | Continue full dose                                             |
| 40 - $<50\text{mL/min}$                  | Cisplatin 50% dose
Capecitabine 75% dose                    |
| 30 - $<40\text{mL/min}$                  | Stop cisplatin, use carboplatin AUC 5
Capecitabine 50% dose |
| $< 30\text{mL/min}$                      | Stop cisplatin, use carboplatin AUC 5
Stop capecitabine     |

For a GFR of 50 to  $<60\text{mL/min}$ , a dose reduction of Cisplatin by 50% may be given if local policy.

Consider dose reduction of 5FU in cases of severe renal impairment (i.e.  $\text{GFR} \leq 10\text{mL/min}$ ).

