### Capecitabine (or 5FU) dose reduction schedule for non-haematological toxicities.

| Toxicity                   | During a course of therapy                                                                                                                                                              | Dose adjustment for next cycle (% of starting dose) |
|----------------------------|-----------------------------------------------------------------------------------------------------------------------------------------------------------------------------------------|-----------------------------------------------------|
| • Grade 1                  |                                                                                                                                                                                         |                                                     |
|                            | Maintain dose level                                                                                                                                                                     | Maintain dose level                                 |
| • Grade 2                  |                                                                                                                                                                                         |                                                     |
| 1 st appearance | Interrupt until resolved to grade 0-1                                                                                                                                                   | 100%                                                |
| 2 nd appearance | Interrupt until resolved to grade 0-1                                                                                                                                                   | 75%                                                 |
| 3 rd appearance | Interrupt until resolved to grade 0-1                                                                                                                                                   | 50%                                                 |

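### 75% capecitabine table, BSA ≤1.38: 650 mg is 81.25% of the 800 mg starting dose, although an exact 75% (600 mg, 4 x 150 mg) can be made

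*Protocol*

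**What the plan says.** Section 8.2.1 of the protocol has three capecitabine tables, by BSA band and tablet count: "Calculated capecitabine dose at dose level 625 mg/m"² for full dose, "Calculated capecitabine dose at dose level 75" per cent, and "Calculated capecitabine dose at dose level 50" per cent. For BSA ≤1.38 they print, per administration and twice daily:

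- full dose: 800 mg (2 x 150 mg + 1 x 500 mg);
- 75% level: 650 mg (1 x 150 mg + 1 x 500 mg);
- 50% level: 450 mg (3 x 150 mg).

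The full dose of 625 mg/m2 is to be rounded "to the nearest achievable dose using 500mg and 150mg tablets". Neither reduced table states its basis or a rounding rule.

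Section 8.4.1 sends patients to the 75% level by three routes:

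- Non-haematological toxicity, where the column is headed "Dose adjustment for next cycle (% of starting dose").
- Haematological toxicity: "Restart with 25% dose reduction cisplatin and capecitabine (or 5FU").
- GFR 40 to <50 mL/min, at baseline or before Day 1: "Capecitabine 75% dose".

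The last two state no basis for the percentage.

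**The concern.** Everyone in the lowest BSA band who starts at full dose takes 800 mg, whatever their exact BSA. If the 75% level means 75% of that dose, the cell should read 600 mg. The printed 650 mg cuts the dose by less than ordered, and it does so in the smallest patients at the moment when toxicity or impaired renal function calls for less drug.

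Tablet size does not force 650 mg. The 50% table already prints 600 mg as 4 x 150 mg (BSA 1.79-1.92), and the 75% table accepts 5 x 150 mg at BSA 1.53-1.78 to reach exactly 750 mg. The two lowest rows of the 75% table also carry the same 650 mg although their starting doses are 800 and 950 mg.

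What is at stake is a dosing instruction, not the design or analysis of the trial.

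**Working it through.** **Inputs.** Full, 75% and 50% doses from the three tables in section 8.2.1; nominal dose 625 mg/m2 twice daily; tablets of 150 and 500 mg.

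**1. Starting-dose basis.** Target = 0.75 x tabulated full dose.

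| BSA band | Full dose (mg) | 75% target (mg) | Printed (mg) | Printed / full | Exact 75% can be made? |
|---|---|---|---|---|---|
| ≤1.38 | 800 | 600 | 650 | 81.25% | yes, 4 x 150; not used |
| 1.39-1.52 | 950 | 712.5 | 650 | 68.4% | no |
| 1.53-1.78 | 1000 | 750 | 750 | 75.0% | yes, 5 x 150; used |
| 1.79-1.92 | 1150 | 862.5 | 800 | 69.6% | no |
| 1.93-2.18 | 1300 | 975 | 1000 | 76.9% | no |
| ≥2.19 | 1450 | 1087.5 | 1150 | 79.3% | no |

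Every dose made from these tablets is a multiple of 50 mg, so of the six targets only 600 and 750 mg can be met exactly. The printed 650 mg is not reproduced on this basis.

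- Reduction given: 1 - 650/800 = 18.75%, against 25%.
- Excess: 650 - 600 = 50 mg per dose; 50/600 = 8.3%; 50 x 2 x 21 = 2100 mg per cycle.

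**2. Actual-BSA basis.** Target = 0.75 x 625 x BSA = 468.75 x BSA.

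At BSA 1.38 the target is 646.9 mg, so 650 mg is reproduced at the top of the band. The midpoint between 600 and 650 is 625 mg, reached at 625/468.75 = 1.333. So 600 mg is the closer dose at BSA ≤1.33 (values from 1.20 checked), and 650 mg is closer at 1.34-1.38.

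| BSA | 650/(625 x BSA) | 600/(625 x BSA) |
|---|---|---|
| 1.20 | 86.7% | 80.0% |
| 1.30 | 80.0% | 73.8% |
| 1.33 | 78.2% | 72.2% |
| 1.34 | 77.6% | 71.6% |
| 1.38 | 75.4% | 69.6% |

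**3. Other cells on the starting-dose basis.** The flagged cell misses its target by 50 mg. Four others miss by more in milligrams, and each has a closer achievable dose:

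- 75%, 1.39-1.52: 650 against 712.5, off 62.5; 750 (5 x 150) is closer.
- 75%, 1.79-1.92: 800 against 862.5, off 62.5; 900 (6 x 150) is closer.
- 75%, ≥2.19: 1150 against 1087.5, off 62.5; 1100 (4 x 150 + 500) is closer. This too is an under-reduction: 20.7% instead of 25%.
- 50%, ≥2.19: 650 against 725 (44.8%), off 75; 750 (5 x 150) is closer.

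**4. How many patients.** The protocol gives no BSA distribution. Assume it is normal with SD 0.20 and a mean between 1.75 and 1.85. Table 1 in section 2.3 reports "4 x dose reductions" among 31 oesophageal patients; take 4/31 as the reduction rate.

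| Mean BSA | Share ≤1.38 | x 420 | x 4/31 |
|---|---|---|---|
| 1.75 | 3.2% | 13.5 | 1.7 |
| 1.80 | 1.8% | 7.5 | 1.0 |
| 1.85 | 0.9% | 3.9 | 0.5 |

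Under these assumptions about 50-56% of the patients in the band have BSA ≤1.33.

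**The case against.** The strongest defence is that the 75% level means 75% of 625 mg/m2. The table titles run in parallel, and the starting-dose wording is one column heading that covers non-haematological toxicity only. A patient may also enter with a GFR of 40 to <50 mL/min (section 4.1.1, criterion 11), go straight to the 75% level and never take 800 mg. For that patient the BSA-based reading is natural. This stands for BSA 1.34-1.38, where 650 mg is the closer dose. It fails at or below 1.33, where 650 mg is too high on either basis. Part of the excess at very low BSA comes from the open-ended band itself: 800 mg is already 106.7% of 625 mg/m2 x 1.20.

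The second defence is that all the tables are coarsely rounded and this cell does not have the largest miss. That is true, and it limits what can be said. What sets this cell apart is that an exact value was available and not taken. Tablet burden does not explain that, given the five-tablet row at 1.53-1.78.

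A reader might infer three stronger things that the documents do not support:

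- That the cell breaks the protocol's rounding rule. That rule is attached only to the 625 mg/m2 dose.
- That every 25% reduction in the protocol is defined against the starting dose. Only the non-haematological table says so.
- That 650 mg is wrong across the whole band on any basis. It is not at BSA 1.34-1.38.

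**Conclusion.** The point holds as a minor dosing-table error, with moderate confidence. For a patient on 800 mg, the 75% cell at BSA ≤1.38 gives an 18.75% cut, and an exact 75% was achievable. Where the starting-dose basis is stated (non-haematological toxicity), 650 mg is too high throughout the band. Where no basis is stated, it is clearly too high only at BSA ≤1.33.

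The scale is about one patient (0.5 to 1.7). That rests on an assumed BSA distribution and on a reduction rate from one small single-centre series that does not name the drug or the level reduced to. Both arms use the same table. Nothing follows for sample size, power, the feasibility count or the survival comparison.

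**What to change.** Change the 75% cell at BSA ≤1.38 to 600 mg: 4 x 150 mg in the morning and 4 x 150 mg in the evening.

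Do not add an unqualified sentence that the reduced tables are based on the starting dose, because the rows at 68.4%, 69.6%, 79.3% and 44.8% would contradict it. Either leave the basis unstated, or say that the tables are based on the tabulated starting dose, rounded to available tablets. In the second case, have pharmacy check the four cells listed in step 3 of the working.

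The cost is one table row, at most one line of text, and a pharmacy memo. There are two clinical downsides:

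- Patients who may have dysphagia would take four tablets instead of two per dose.
- At BSA 1.34-1.38, 600 mg is only 71.6% down to 69.6% of the BSA-based full dose. This is partly because 800 mg is itself only 92.8% of that dose at 1.38. Section 8.4.1 does not allow a dose reduced for toxicity to be raised again, so the lower dose would persist.
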